## Abstract

**Background:**

Cancer survivors frequently report a range of unmet psychological and supportive care needs; these often continue after treatment has finished and are predictive of psychological distress and poor health-related quality of life. Web-based interventions demonstrate good efficacy in addressing these concerns and are more accessible than face-to-face interventions. *Finding My Way* (FMW) is a web-based, psycho-educational, and cognitive behavioral therapy intervention for cancer survivors developed in Australia. Previous trials have demonstrated that *FMW* is acceptable, highly adhered to, and effective in reducing the impact of distress on quality of life while leading to cost savings through health resource use reduction.

**Objective:**

This study aims to adapt the Australian *FMW* website for a UK cancer care context and then undertake a single-blinded, randomized controlled trial of *FMW UK* against a treatment-as-usual waitlist control.

**Methods:**

To an extent, our trial design replicates the existing Australian randomized controlled trial of *FMW.* Following a comprehensive adaptation of the web resource, we will recruit 294 participants (147 per study arm) from across clinical sites in North West England and North Wales. Participants will have been diagnosed with cancer of any type in the last 6 months, have received anticancer treatment with curative intent, be aged ≥16 years, be proficient in English, and have access to the internet and an active email address. Participants will be identified and recruited through the National Institute for Health Research clinical research network. Measures of distress, quality of life, and health economic outcomes will be collected using a self-report web-based questionnaire at baseline, midtreatment, posttreatment, and both 3- and 6-month follow-up. Quantitative data will be analyzed using intention-to-treat mixed model repeated measures analysis. Embedded semistructured qualitative interviews will probe engagement with, and experiences of using, *FMW UK* and suggestions for future improvements*.*

**Results:**

The website adaptation work was completed in January 2021. A panel of cancer survivors and health care professionals provided feedback on the test version of *FMW UK.* Feedback was positive overall, although minor updates were made to website navigation, inclusivity, terminology, and the wording of the *Improving Communication* and *Sexuality and Intimacy* content. Recruitment for the clinical trial commenced in April 2021. We aim to report on findings from mid-2023.

**Conclusions:**

Replication studies are an important aspect of the scientific process, particularly in psychological and clinical trial literature, especially in different geographical settings. Before replicating the *FMW* trial in the UK setting, content updating was required. If *FMW UK* now replicates Australian findings, we will have identified a novel and cost-effective method of psychosocial care delivery for cancer survivors in the United Kingdom.

**Trial Registration:**

International Standard Randomized Controlled Trial Number (ISRCTN) 14317248; https://www.isrctn.com/ISRCTN14317248

**International Registered Report Identifier (IRRID):**

DERR1-10.2196/31976

## Introduction

### Background

Cancer survivorship rates in the United Kingdom have increased such that up to 57% of cancer patients in the United Kingdom can now expect to survive for 10 years [1]. However, there is regional discrepancy, and survival rates differ across geographic regions and treatment center catchment areas. Recently published screening studies suggest a prevalence of distress of up to 41.5% in adolescents and young adults [2] and 46% in adult [3] cancer populations. Anxiety, depression, and other psychological comorbidities significantly impact quality of life [4]. If left untreated, distress can escalate [5], and a pooled analysis of 163,363 cancer survivors demonstrated that distress in some cancer groups predicted higher mortality risk, even after controlling for age, sex, education, socioeconomic status, BMI, smoking, and alcohol intake [6]. Our own work in people diagnosed with the four most common cancers demonstrates that cognitive and emotional responses to diagnosis can predict distress [4] and that psychological variables, such as psychological flexibility, are predictive of distress-related outcomes *independent* of clinical and sociodemographic characteristics [7]. Unmet psychological and supportive care needs are prevalent in cancer survivors [8-11]; we found that 54% of hematological patients report five or more unmet supportive care needs [10], and 46% of colorectal patients report at least one specific psychological need [12]. Therefore, there is a crucial need to develop effective interventions to manage psychological distress in cancer survivors.

A recent review of psychological interventions for patients with cancer [13] concluded that although cognitive behavioral therapy remains the gold standard treatment choice, we need more methodologically robust research to determine efficacy and scope for implementation. There is an excess of small-scale studies where fully powered trials exploring moderators and mediators of effects are needed. Research in non–breast cancer populations is recommended, along with the inclusion of health economic outcomes, to provide powerful data for clinical service commissioners. Given the high cost and time invested in developing new intervention content and delivery formats, one effective strategy is to adapt *existing* interventions rather than waste finite resources to develop novel and competing interventions. Furthermore, replication studies are important to demonstrate consistency and generalizability of outcomes and are recommended in response to the replication crisis in psychology [14].

A recent systematic review highlighted that one of the top barriers to accessing psychosocial support identified by patients with cancer is difficulty with transport to the health service delivery center [15], although other types of access issues have been reported elsewhere. To overcome this barrier, recent research has increasingly investigated the feasibility and efficacy of web-based psychosocial interventions for patients with cancer [16]. Web-based delivery methods are also recommended to overcome the expense of delivering psychological support [17-19]. Given the recent increases in home-based internet access in the United Kingdom, especially through the rapid development and uptake of smartphone and tablet technologies [20], web-based interventions may address access issues by widening the potential pool of beneficiaries [21]. They also overcome the stigma associated with overtly seeking psychological support [22], and (as demonstrated through the current COVID-19 pandemic) are a way to ensure continuation of service where there may be barriers to continued face-to-face care [23]. Digital psychosocial interventions confer many potential benefits, including greater convenience, reduced burden on patients with cancer and caregivers, and reduced resource use and health care costs, as compared with traditional face-to-face interventions [24]. However, most clinically measurable differences associated with web-based psychosocial interventions for this population fail to meet statistical significance, a phenomenon likely attributable to study design rather than a lack of real effect [16]. In addition, there is a need to identify treatment components involving active user engagement with web-based exercises to mitigate the lack of face-to-face interaction.

One of the most promising web-based interventions for cancer survivors is *Finding My Way* (FMW), developed by Beatty et al [25] in Australia. FMW is the second iteration of a six-module, web-based, self-guided intervention, initially titled *Cancer Coping Online* [26]. It uses psycho-educational and cognitive behavioral therapy–based theoretical frameworks and includes exercises from third-wave approaches, for example, mindfulness and values clarification work exercises. Early pilot work demonstrated benefits for physical functioning and distress outcomes [18]. Although between-group differences were not replicated in a recent, larger, randomized controlled trial (RCT) [27], this trial compared the intervention group with a low-dose active control group (identical psychoeducation and video-based content), with both groups reporting reductions in distress over time. As such, the lack of significant between-group findings may be related more to the overlap of content between treatment groups rather than a lack of efficacy in the web-based intervention group. This recent RCT found significantly better emotional functioning and lowered health care use in the FMW arm, demonstrating both (1) that distress had less functional impact on quality of life and (2) health service cost reduction [27]. Adherence was also high [26]. A number of replication studies of FMW are underway across the world, and FMW has been adapted for women with advanced breast cancer [28], demonstrating the flexibility of the program for different demographic groups and clinical contexts. As such, FMW is a good candidate for effective support in the UK cancer care setting, but some adaptation was necessary before implementation.

### Objective

This paper reports on our work undertaken to adapt the intervention, and the protocol for the ongoing RCT, which tests its efficacy in a UK National Health Service (NHS) setting. We aim to test (1) whether outcome effects are replicated or improved and (2) whether intervention uptake, use, and acceptability meet feasibility thresholds for implementation in standard care.

## Methods

### Trial Design

We will conduct a single-blinded RCT of FMW UK compared with treatment-as-usual control. Mixed methods data collection—using self-report questionnaires, quantitative clinical data extraction, and in-depth interviews—will be undertaken to investigate efficacy and acceptability. Where possible, trial design and outcomes replicate the key features of the Australian RCT of FMW by Beatty et al [27].

All aspects of study design and governance are planned to involve the expert voices of people affected by cancer as active partners in the research study. The University of Chester hosted the study with scrutiny provided by a trial steering group comprising grant coapplicants (including a cancer survivor coapplicant), the local research team, a patient, a caregiver, and a health care professional stakeholder representative. The steering group meets twice per year, with a smaller project management group meeting bimonthly to provide operational oversight. The funder peer-review report is presented in Multimedia Appendix 1.

### The FMW UK Intervention

The FMW UK intervention is designed as a six-week, self-administered, modularized, web-based program. Written and video-based information about a range of cancer care topics and the provision of psychological intervention materials are supplemented with testimonials from cancer survivors sharing their experiences and advice. Interactive exercises, including worksheets, assessment tools, and prerecorded self-guided mindfulness meditations are included; these experiential components are likely to boost efficacy [27]. The modules, released one per week, address common psychosocial concerns and unmet needs among cancer survivors and are structured around (1) treatment and communication with treatment teams; (2) coping with physical symptoms and side effects; (3) managing distress; (4) challenges to identity, body image, and sexuality; (5) social support and family concerns; and (6) issues that arise after treatment. On first accessing the site, users are prompted to choose the order in which they wish to access modules to meet their self-determined need priorities. A booster module is released one month after completion, which recaps program content and signposts back to earlier modules.

### Contextual Adaptation

We began our adaptation of FMW with our local research team reviewing the information provided to determine which aspects needed to change for the UK cancer care setting. This included referencing standard care pathways and services available to patients with cancer in the United Kingdom and adapting some terminology to avoid confusion. We reviewed all website content to identify Australian-specific resources and treatment information and then worked with our steering group (including academics, clinicians, and patient and caregiver representatives) to systematically identify equivalent British information and signposting resources with which to replace them. Our adaptation plan was approved by the trial steering group.

Question schedule for video interviews with cancer survivors to create the Finding My Way UK intervention content.Question scheduleWhat issues came up for you after diagnosis (and during treatment) in terms of making decisions about treatment, or when discussing things with your medical treatment team?During treatment, what was your most pressing physical need/concern?During treatment, what was your most pressing emotional need/concern?Some people find that many of their roles change during treatment, and that they aren’t able to do the tasks and activities they usually do, which then affects the way they feel about themselves. During treatment, how did your roles change and how did this affect you?During treatment, what was your most pressing social need? What surprised you?What things were challenging for you with your family life?If you could give one piece of advice to another person with cancer, what would it be?Over the process of treatment, what was the most confusing issue for you?What did you do to mark the end of your treatment?What advice would you give to other cancer survivors about staying healthy?Some people say that having cancer gave them an opportunity to learn something new about life or themselves. What is the one learning experience you had that you would not have had if you did not have cancer?Were there any other questions you thought we should have asked?

Video interview participants (survivors and health care professionals) were reimbursed for their time and travel expenses, as is good practice for patient and public involvement in health research [29]. All participants signed a consent form to permit the ongoing use of their video content after the trial was complete. Given that these interviews took place during the COVID-19 pandemic, a rigorous health and safety assessment was undertaken, and appropriate infection control measures were implemented. Video recordings (and later editing work) were undertaken by the research team, given the difficulties inherent in commissioning this work to an external company through the intermittent implementation of COVID-19 related social distancing in the United Kingdom during this time.

### Evidence Review

Given that the Australian FMW content was last updated in 2013, we reviewed all research claims made throughout the website content and conducted literature reviews to identify which claims were still upheld by recent research. We subsequently updated the references for some evidence statements and edited claims that were no longer conclusively supported by the current evidence base. In brief, this includes the following:

De-emphasizing the strength of claims made about the benefits of emotional expression and therapeutic writing [30,31].Updated references in relation to benefit finding and positive adjustment [7].Updated reference to support our recommendation for the benefits of mindfulness-based exercises [32].Inclusion of more recent references in relation to the impact of dyadic influences on adjustment between patients and their partners [33] and in relation to the benefits of information on distress levels in close others of people being treated for cancer [34].Reframing of claims made about the benefits of religious and spiritual beliefs to confirm that these may be helpful for those with existing beliefs, but that we are not seen as advocating a change in practices or beliefs.

### Web Hosting and User Testing

We commissioned an independent web design company to adapt the original FMW web-based framework for our purposes. The website was designed using *Wordpress v.5.7.1* (WordPress Foundation) and was hosted through *Kinsta.* Videos are uploaded to *YouTube* with embedded links provided at relevant points on the website. The videos are not publicly listed to prevent access outside of the trial, and the FMW UK website is restricted to only those with a username and password provided by our team.

Once an initial test website had been created, we recruited a panel of four cancer survivors and three health care professionals to provide user feedback, each of whom was financially compensated for their input. Cancer survivors were identified from our initial advertisement for video interview participants, and health care professionals (oncology and psychology-based) were identified from existing professional networks. Additional user testing was performed by the trial steering group. Where relevant, feedback was integrated into a final website update (see the *Results* section) before recruitment commencing.

### Participants

#### Sample Size Calculation

Calculations were based on the primary outcome of change in cancer-specific distress between the two patient groups. The original FMW RCT sample size calculation [27] used a standardized effect size of 0.35 and an SD of 4 units, which equates to an absolute change in cancer distress scores of 1.4 units. This study observed a larger than expected SD and we propose a sample size based on a conservative estimate of the residual SD of 7 units accordingly (but keeping the clinically relevant difference at the aforementioned 1.4 units). The correlation between successive measurements on the same patient is assumed to be high, and so a conservative *r*=0.70 was used. Sample size calculations were performed assuming a paired two-tailed *t* test using the derived SD of the change in the primary outcome of 5.42. Assuming a patient attrition of 20% and α of .05, 294 patients (147 per study arm) are required for a statistical power of 80% [35]. We will allow up to 30% overrecruitment to mitigate the effects of missing data and to allow for at least minimal recruitment of less common cancer types.

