### Analysis

The analysis plan matches the Australian FMW RCT [27] as closely as possible. Members of the research team involved in the analysis will be blinded to the condition allocation until the end of the trial. First, we will conduct data cleaning to ensure that all data values are possible and plausible. Errant data entries will be deleted from the final analysis data set and missing data will be handled using either prorating or imputation methods as is (1) appropriate to the collected data and (2) congruent with the specific scoring instructions for the psychometric measure from which there is a missing response.

Descriptive statistics will be used to provide sample characteristic information and to identify any potentially prognostic demographic or clinical covariates. Inferential statistical analyses are powered to undertake mixed model repeated measures analyses to examine intervention effects on change from baseline to follow-up for each outcome, using intention-to-treat analysis. Two models will be run for each: (1) unadjusted, accounting for covariance of baseline measures of outcomes and (2) fully adjusted, controlling for all potential confounding variables assessed. Where possible and adequately powered, we will include potential confounders in our analyses and evaluate the effects of missing data using sensitivity analysis. Cohen *d* effect sizes reflect intervention effects, and clinically significant changes will be assessed using reliable change indices. The health care use outcome will be summarized descriptively for activity counts and cumulative costs estimated by assigning unit costs to units of activity. Cost summaries are derived from discrete payer perspectives. Generalized linear models will be used to adjust for the same confounding variables as in the efficacy analysis. All quantitative data analyses will be undertaken in R software (R Foundation for Statistical Computing) [50] where possible, with any supplementary analyses conducted in IBM SPSS as appropriate*.*

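### The 147 per arm comes from a paired, single-group t test, so the reported calculation does not support 80% power; between-arm power at a single follow-up visit is about 57% with baseline adjustment

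*Protocol article*

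**What the plan says.** The Sample Size Calculation section of the Protocol article opens with a comparison of two arms: "Calculations were based on the primary outcome of change in cancer-specific distress between the two patient groups". Its inputs are a target difference ("keeping the clinically relevant difference at the aforementioned 1.4 units"), a spread ("a conservative estimate of the residual SD of 7 units accordingly") and a within-patient correlation ("so a conservative *r*=0.70 was used"). It then names the test: "Sample size calculations were performed assuming a paired two-tailed *t* test using the derived SD of the change in the primary outcome of 5.42". With two-sided alpha 0.05 and 20% attrition, it concludes that "294 patients (147 per study arm) are required for a statistical power of 80" per cent. Over-recruitment of up to 30% is permitted, for missing data and rarer cancer types.

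Trial Design describes a parallel-group randomised trial against treatment as usual. The Analysis section says "Inferential statistical analyses are powered to undertake mixed model repeated measures analyses" of change from baseline to follow-up. It plans two models, and even the one it labels unadjusted takes baseline scores into account.

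**The concern.** A paired t test on change scores asks whether the mean change in one group of patients differs from zero. This trial asks whether mean change differs between two independent groups. The variance of that difference is the sum of two arm variances, so for the same target difference and SD each arm must be twice the size of the single paired sample. If the paired sample size was assigned to each arm without doubling, the 80% does not describe the comparison the trial will make.

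The point matters because the article presents the trial as a replication. Its Background notes that the earlier, larger trial found no between-group difference in distress, and it calls for fully powered studies. If power for the difference called clinically relevant is well below 80%, a null result would say less about efficacy than readers of the stated figure would suppose.

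**Working it through.** **Inputs, all from the Sample Size Calculation section:** difference 1.4; SD 7; r = 0.70; two-sided alpha 0.05 (z = 1.96); power 80% (z = 0.8416); attrition 20%; 147 per arm.

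**1. Reproducing the plan's figure.**
- SD of change = 7 × √(2 × (1 − 0.70)) = 5.42, as stated.
- Paired n = ((1.96 + 0.8416) × 5.42 / 1.4)² = 117.6.
- After attrition: 117.6 / 0.80 = 147.0, the stated size of each arm.

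The exact paired t test needs 120, or 120 / 0.80 = 150, which is close. The word paired is therefore not a slip of the pen; the arithmetic follows it.

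**2. Two-sample variants with the same difference, alpha and power.** None gives 147 per arm.

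| Calculation | Completers per arm | Randomised per arm (÷ 0.80) |
|---|---|---|
| Change scores, SD 5.42 | 236 | 295 |
| Baseline-adjusted, SD 7 × √(1 − 0.70²) = 5.00 | 201 | 252 |
| Change scores, one-sided | 186 | 233 |
| SD 7, no use of baseline | 393 | 492 |
| The earlier trial's SD of 4 | 129 | 162 |

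For change scores the unrounded need is 2 × 117.6 = 235.3 completers per arm, and 235.3 / 0.80 = 294 per arm. On that analysis the plan's total equals the number needed in each arm.

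**3. Power at one follow-up visit with 294 randomised.** Completers per arm: 147 × 0.80 = 117.6, taken as 118.
- Change scores: SE = 5.42 × √(2/118) = 0.706; 1.4 / 0.706 = 1.98; power 51% (noncentral t also 51%).
- Baseline-adjusted: SE = 5.00 × √(2/118) = 0.651; 1.4 / 0.651 = 2.15; power 58% (noncentral t 57%).
- Detectable with 80% power: 2.80 × 0.706 = 1.98 units on change scores; 2.80 × 0.651 = 1.82 units with baseline adjustment.

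**4. Over-recruitment.** 294 × 1.3 = 382 randomised; 382 × 0.80 / 2 = 153 completers per arm. Single-visit power is about 62% on change scores and 69% with baseline adjustment.

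**5. A contrast averaged over the four post-baseline visits.** The article does not specify this. It needs two assumptions of mine: a constant 1.4-unit effect from mid-intervention onward, and a correlation structure. With 118 per arm and baseline adjustment:
- Compound symmetry at 0.70: variance = 49 × ((1 + 3 × 0.70)/4 − 0.70²) = 13.97, SD 3.74, power about 82%.
- AR(1) decay from 0.70: SD 4.86, power about 60%.

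**6. Sensitivity to the meaning of 7.** The derivation of 5.42 treats 7 as the SD at one time point, although the text calls it a residual SD. If 7 were already net of baseline, r should not be applied again, and single-visit power with SD 7 and 118 per arm would be about 33%.

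**The case against.** The strongest reply is that the planned analysis is a repeated-measures mixed model over several visits, not a test at one visit. Step 5 shows that an averaged contrast could reach about 82%, so a reader who infers that the trial's power simply is 51% to 57% goes further than the document allows. This stands as a limit on the claim: the article names no single primary visit, and the figures hold for a single-visit contrast. It does not rescue the stated 80%. The article names no averaged contrast, its calculation did not use one, and the same contrast has about 60% under AR(1). The uncertainty runs downward too, since under AR(1) the correlation with baseline at a late visit would be below 0.70.

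Three narrower replies also have merit.
- The planned models adjust for baseline, so the relevant single-visit power is 57% rather than 51%, and the total for 80% power is about 504 (2 × 252) rather than 590 (2 × 295).
- A mixed model uses partial data from patients who drop out, so 118 per arm is a cautious figure. With no loss at all (147 per arm), single-visit power is still only 67% with baseline adjustment and 60% on change scores.
- A reader might infer that the mixed model was never powered. That is not established: Dissemination Plans refers to a full protocol held elsewhere, which is not shown. What can be said is that the calculation reported in the article does not support the statement.

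**Conclusion.** The power statement is wrong as written. The question is between arms, the sample size is that of a paired test in one group, and the arithmetic reproduces only on that basis. For 294 randomised with 20% attrition, SD 7 at a single time point, r = 0.70 and a 1.4-unit difference, the between-arm comparison at one follow-up visit has about 57% power with the planned baseline adjustment. That is some 23 percentage points below the stated 80%. The optional over-recruitment does not close the gap at a single visit.

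The finding does not show that every contrast the mixed model could yield is underpowered, nor that more patients must be enrolled. The averaged-contrast range and the 33% figure rest on assumptions that the article does not make, and serve only to show how far the answer depends on choices left open.

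**What to change.** 1. In Sample Size Calculation, replace the paired t test with a two-sample, baseline-adjusted calculation (ANCOVA or MMRM) for a named primary contrast: either one visit or a stated average over visits, with its assumed correlation structure and effect pattern.
2. Restate power and detectable difference for 294 randomised. For a single visit these are about 57% for 1.4 units and about 1.8 units at 80% power. If an averaged contrast is chosen, show its power across plausible correlation structures rather than under the most favourable one.
3. State whether 7 is the raw SD at one time point or a residual SD net of baseline, and make the use of r = 0.70 consistent with that.
4. In Analysis, reword the statement that the mixed models are powered so that it refers to the named contrast and its recomputed power.

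This is a change of wording and figures that adds no patients. The cost is a less favourable stated power.
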